**Data analysis:**

The comparisons of pain and other continuous outcomes will be done employing a repeated measures mixed model incorporating terms of treatment, time, and respective baseline values as covariates. We will also assess the effects of potential confounders or interaction with treatment by covariates, including age, sex, BMI, disease severity, comorbidities, health status, and use of pain medications. A two-sided p-value less than 0.05 will be considered to indicate the statistical significance, and the results will be shown as the between-group differences with 95% confidence intervals (95% CIs) of the differences.

We will explore the role of clustering effects in the trial by performing a sensitivity analysis examining the implications of clustering by the instructor by adding an instructor random effect to our mixed-effects model.

We will also perform an exploratory analysis to investigate whether the presence or absence of neuropathic pain, as assessed by the painDETECT questionnaire, is a potential moderator that influences response to treatment for the primary outcome at 12 weeks. To assess the moderation of the effect by painDETECT (binary moderator), an interaction term between the randomised group and the potential moderator will be included in outcome regression models.

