**Abstract:**

Osteoarthritis (OA) is one of the major causes of pain and disability in the Australian population. Knee OA is the most common form of OA. Currently, there is no disease-modifying treatment available for knee OA.

Knee OA can be categorised by its manifestation characteristics at the structural and symptomatic levels. While biomarkers including MRI markers have enabled stratification of OA patients based on structural abnormalities, analyses of data from large observational studies and clinical trials have suggested the existence of distinct pain phenotypes (1-3) in knee OA. The pain phenotype can be defined as a subtype of OA that shares a distinct underlying pain mechanism. The pain phenotype of OA is complex and may be influenced by psychological factors (e.g. depression, pain-related fear, and anxiety) (4-6) and central pain processing (central sensitisation) (7, 8). The common discrepancies observed between the symptom severity and structural findings of knee OA may also be attributed to these factors (9). Pain is maintained by nociceptive, central, or neuropathic inputs and there is evidence of these in OA (10-12). Various studies using painDETECT have reported a 5-50% prevalence of neuropathic pain type in knee OA populations (10, 13).

Current pharmacological treatments for patients with symptomatic OA are palliative and primarily focus on pain relief. There is evidence that non-pharmacological treatments, such as exercise therapy (aerobic, muscle-strengthening, etc.) improve pain, function, depression, and quality of life (QoL) in people with OA (14). However, many studies are of low quality and had a high risk of bias, mainly due to comparing to a usual care arm (14-16). Increasing evidence demonstrates that neuropathic pain may contribute to the pain experience for a subgroup of OA patients. Therefore, it is possible that OA patients will show greater benefit from centrally-acting non-pharmacological therapies such as yoga (7, 17-20).

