Yoga is a mind-body therapy, and the physical component of yoga provides exercise that is consistent with recommendations for knee OA (21, 22), while the mind component has the potential to increase psychological well-being and reduce stress (23, 24), which can influence central sensitisation. Only a few studies have evaluated the effect of yoga in patients with OA. Current guidelines for the treatment of knee OA suggest a 'conditional recommendation' for yoga as an adjunctive form of exercise, and only for short-term management. The guidelines highlighted the lack of evidence and the poor quality of the existing evidence. A systematic review of yoga intervention studies (including RCT and non-RCT) in OA reported a significant effect on pain and mobility. However, they reported a lack of data on QoL and mental health (25). Small sample sizes, shorter duration of follow-up, lack of an active comparator, and poor methodological quality of previous studies prevent definitive conclusions.

The primary aim of this 24 weeks randomised controlled trial (RCT) is to investigate the effectiveness of a 12-week group-based *yoga program* (12 weeks of yoga (3x/week)) compared to a group-based *strengthening exercise program* (3x/week) on the knee pain (assessed using VAS) in knee OA patients over 12 weeks. We hypothesise that a group-based yoga program will be superior to the group based strengthening program.

A secondary aim is to assess whether the effects are moderated by the presence of neuropathic pain such that individuals with neuropathic pain respond better to a yoga program compared to strengthening exercise program than those without neuropathic pain.

If successful, yoga can be easily implemented as a complementary treatment along with conventional treatment to improve the management of knee OA.

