### **Randomisation and blinding:**

Allocation of participants in a 1:1 ratio to either a 12-week *yoga program* or *strengthening exercise program* will be based on computer-generated random numbers prepared by a statistician with no involvement in the trial. Code-break for the full randomisation schedule will be maintained by the administering institute.

The assessors will be blinded to treatment allocation for objective outcome measures. Allocation concealment and blinding will be ensured by having two research nurses coordinate the trial. Assessments will be taken by the research nurse blinded to the group allocation.

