**Primary outcome:**

Change in knee pain assessed by VAS for over 12 weeks. Pain will be evaluated at each time point using a 100mm VAS and asked: “On this line, how would you rate your overall average knee pain in the last one week”? For knee pain assessed using VAS, terminal descriptors will be 0mm = no pain, 100mm = worst pain possible.

**Secondary outcomes:** (overall change from baseline to week 12 and overall change from baseline to week 24 are separate outcomes)

1. Change in VAS knee pain over 12 weeks in patients with painDETECT>12
2. Change in VAS knee pain over 24 weeks.
3. Change in WOMAC knee pain, WOMAC stiffness, and WOMAC knee function over 12 weeks and over 24 weeks.
4. Change in physical function as assessed by 30s Chair Stand Test, 40m Fast Walk Test and Stair Climb Test over 12 and over 24 weeks
5. OMERACT\_OARSI responders (meeting responder criteria) at week 12, and 24 weeks
6. Change in biomarker (urinary CTX-II, serum COMP, and serum hyaluronan) and systemic inflammatory markers (hs-CRP, IL-6, TNF- $\alpha$ ) over 12, and over 24 weeks
7. Change in Patient Health Questionnaire (PHQ-9) scales over 12, and over 24 weeks
8. Change in patient global satisfaction score over 12, and over 24 weeks
9. Change in painDETECT scores over 12, and over 24 weeks
10. Change in leg muscle strength (quadriceps) over 12, and over 24 weeks
11. Change in gait speed from baseline to week 12 and baseline to 24 weeks

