***Sample Size calculation:***

Our power calculations are based on a sample size that can document the minimal clinically important difference (MCID) in VAS knee pain superior to yoga compared to strengthening exercise. Based on the MCID of 15mm in VAS pain [a numerical scale ranging from 0 (no problem) to 100 (maximum problem)], two-sided significance level of 0.05, 90% power and SD of VAS pain change 22.5, we will need a total of 98 participants. Assuming a worse scenario of 20% dropout, we will need 126 participants.

The above sample size will allow us to detect a non-inferiority of yoga with strengthening exercise. Non-inferiority would be declared if the mean change in knee pain (assessed using VAS) in the yoga group was not significantly worse than the mean change in the strengthening exercise group, within a pre-stated margin of non-inferiority ( $\Delta$ ), in this case, set at 10 mm. Overall, 126 participants will give us 80% power to detect the non-inferiority of yoga compared with strengthening exercise.

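### Moderation by neuropathic pain is tested only with a yes/no painDETECT split, which is imprecise, beside a painDETECT>12-only outcome that cannot show moderation; add the continuous baseline score

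*Combined protocol and SAP*

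**What the plan says.** The Abstract of the protocol sets the moderation aim as whether patients with neuropathic pain "respond better to a yoga program compared to strengthening exercise program than those without neuropathic pain". The section on study aims words it as a question about the presence of neuropathic pain.

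Three parts of the documents bear on how this is analysed:

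- **SAP, Data analysis.** An analysis labelled exploratory examines presence or absence of neuropathic pain as a moderator of week-12 knee pain, as follows: "To assess the moderation of the effect by painDETECT (binary moderator), an interaction term between the randomised group and the potential moderator" is to be included in the regression models. The cut that defines the two groups is not given there.
- **Protocol, secondary outcomes, item 1** (item 3 in the SAP list). "Change in VAS knee pain over 12 weeks in patients with painDETECT>12". No matching outcome is listed for patients at 12 or below, and neither list says that the classifying score is the baseline one.
- **Protocol, Statistical Analyses.** painDETECT is not among the covariates named for interaction with treatment.

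The schedule of assessments collects painDETECT at baseline, week 12 and week 24, and change in the score is itself a secondary outcome. The graded baseline score is therefore available, but no analysis uses it as a moderator. Power is given for the main comparison only.

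**The concern.** An interaction is estimated much less precisely than a main effect, and splitting a graded score usually makes this worse. In a trial sized only for its main comparison, the moderation result may come with an interval too wide to be useful, although the data for a more efficient analysis are in hand.

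The painDETECT>12 outcome raises a separate matter of logic. The aim compares two treatment effects, and a test inside one stratum estimates only one of them. A significant result there could be taken as a special benefit in neuropathic pain when patients at 12 or below benefit just as much. A non-significant result could be taken as absence of moderation when the stratum is simply small.

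**Working it through.** **Inputs from the documents**

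- SD and main sample size: "two-sided significance level of 0.05, 90% power and SD of VAS pain change 22.5, we will need a total of 98 participants" (protocol, Sample Size calculation).
- Effect: "Based on the MCID of 15mm in VAS pain" (same section).
- Recruitment: "Assuming a worse scenario of 20% dropout, we will need 126 participants". This leaves 126 × 0.8 = 100.8, so about N = 100 analysed.
- Allocation: 1:1.
- Share above the cut, p: "Various studies using painDETECT have reported a 5-50% prevalence of neuropathic pain type in knee OA populations" (Abstract). The cut behind that range is not stated. I assume that it applies to painDETECT>12 and show 50%, 25% and 5%.

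**The plan's own figure.** Per arm, n = 2 × (1.960 + 1.282)² × 22.5² / 15² = 47.3, rounded up to 48, or 96 in total. With the t distribution, 48 per arm gives 89.8% power and 49 per arm gives 90.4%, so the stated 98 is reproduced. Then 98 / 0.8 = 122.5, or 123, close to the stated 126.

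**Binary interaction**

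- SE = 22.5 × √(4/(Np) + 4/(N(1−p))).
- At p = 0.5: 22.5 × √(4/50 + 4/50) = 9.0 mm.
- At p = 0.25: 22.5 × √(4/25 + 4/75) = 10.4 mm.
- At p = 0.05: 22.5 × √(4/5 + 4/95) = 20.6 mm.
- Power for a 15 mm difference in effects is Φ(15/SE − 1.96) plus a negligible opposite tail.
- The difference detectable with 80% power is (1.96 + 0.84) × SE.

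**Information lost by the cut.** For a normal score and linear moderation, the efficiency of the split is φ(z)² / (p(1−p)), where z is the normal quantile that cuts off the upper share p. This is 0.637, 0.539 and 0.224 at the three prevalences.

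**Continuous score under the same truth**

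- Scale the linear moderation so that the two strata differ by 15 mm in mean effect. The strata means lie φ(z)/(p(1−p)) SDs apart: 1.60, 1.69 and 2.17.
- The slope is then 15 divided by that gap: 9.40, 8.85 and 6.91 mm per SD of the score.
- Its SE is 2 × 22.5 / √100 = 4.5 mm.
- Power is Φ(slope/4.5 − 1.96).

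| Share above cut | Binary SE (mm) | Detectable at 80% (mm) | Binary power, 15 mm | Information lost | Continuous power |
|---|---|---|---|---|---|
| 50% | 9.0 | 25 | 38% | 36% | 55% |
| 25% | 10.4 | 29 | 30% | 46% | 50% |
| 5% | 20.6 | 58 | 11% | 78% | 34% |

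**Sensitivity to skew.** With gamma-distributed scores (shape 1, 2 and 4), the loss at the same three prevalences runs from about 36% to 65%.

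**Effect within painDETECT>12.** The stratum would hold about 5 to 50 of the 100 analysed. SE = 22.5 × √(4/(Np)) is 20.1 mm at 5% and 6.4 mm at 50%, giving about 12% to 65% power for 15 mm. That power is for an effect different from zero, not for one different from the effect in other patients.

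**The case against.** The strongest reply is that the plan already contains the right test. The aim is worded as presence against absence, and a group-by-moderator interaction across both strata matches it. The SAP assigns moderation to that interaction and not to the painDETECT>12 outcome, and it calls the analysis exploratory. A slope on the continuous score answers a somewhat different question. All of this stands. It is why the score should be added and should not replace the binary term. A reader might infer that the plan cannot answer its moderation question; the documents do not support that.

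The loss figures can also be challenged. They need a normal score, linear moderation, and the cited prevalence range applying to this cut in a population selected for VAS pain of at least 40 mm. None of these is established in the documents. If moderation acts at a threshold, the split need lose nothing. This stands too, so the figures are conditional.

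Further, 15 mm is the plan's benchmark for the main effect, and no target is set for an interaction. The SD of 22.5 mm takes no account of baseline adjustment or repeated measures, so the SEs are probably somewhat large. That affects both codings alike and leaves their comparison intact.

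The exploratory label does not settle the matter. The same question is a secondary aim elsewhere, and the painDETECT>12 outcome sits among the secondary outcomes without that label.

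**Conclusion.** The point holds as one of precision and reporting, not of a wrong target. On the plan's SD, about 100 analysed and 5% to 50% above the cut, the binary interaction has about 11% to 38% power for a 15 mm difference in effects. Under linear moderation of a roughly normal score, the continuous analysis raises this to about 34% to 55%.

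Two stronger readings should be resisted. One is that the binary test has almost no chance of success, which fits only the 5% end of the range. The other is that the continuous score cures the lack of power: it stays below 80% throughout, so estimates with 95% CIs matter more than p-values.

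One part needs no numerical assumption. The painDETECT>12 result on its own cannot show moderation, because it contains no comparison with patients at 12 or below.

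**What to change.** - In the SAP's Data analysis section, keep the binary interaction and define it as baseline painDETECT >12 versus 12 or less.
- Add treatment by continuous baseline painDETECT to the primary mixed model at week 12. Show the treatment effect with its 95% CI across the score, with a spline check of linearity.
- Reword the painDETECT>12 outcome so that both strata are reported beside the interaction estimate, and state that the >12 result alone is not evidence of moderation.
- Give the moderation question one status, secondary or exploratory, in the aims, the outcome lists and the analysis section.
- The SAP document also describes analyses already carried out for the manuscript, so label the continuous-score model as additional to the plan.

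The cost is one model term and a few lines of wording, with no new data. The downside is one more analysis to report, and a linear interaction is assumed unless the spline check contradicts it.

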**Sample size calculation.**

Our power calculations are based on a sample size that can document the superiority of yoga compared to strengthening exercise by an amount that meets the minimal clinically important difference (MCID). Based on the MCID of 15 mm in VAS pain (a numerical scale ranging from 0 (no problem) to 100 (maximum problem)), the two-sided significance level of 0.05, 90% power, and SD of VAS pain change 22.5, we will need a total of 98 participants.

Assuming a scenario of around 20% dropout, we will need 126 participants. The above sample size will allow us to detect a non-inferiority of yoga with strengthening exercise. Non-inferiority would be declared if the mean change in knee pain (assessed using VAS) in the yoga group was not significantly worse than the mean change in the strengthening exercise group, within a pre-stated margin of non-inferiority (D), in this case, set at 10 mm. Overall, 126 participants will give us 80% power to detect the non-inferiority of yoga compared with strengthening exercise.

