### **SAP as described in the approved version of protocol.**

#### **Statistical consideration**

Hypothesis, primary endpoints (i.e., primary outcome variables), and secondary endpoints

Research hypothesis:

Primary alternative hypothesis: Yoga program will be superior to strengthening exercise program on reducing knee pain (assessed using VAS) over 12 weeks in knee OA patients.

Secondary alternative hypothesis: Yoga program will improve secondary outcomes (namely VAS knee pain over 24 weeks, WOMAC pain, WOMAC function, WOMAC stiffness, OMERACT-OARSI responders, patient global assessment, painDETECT score, Depression (assessed by patient health questionnaire), quality of life (AQoL-8D and EQ-5D-5L), leg muscle strength, core physical performance measures (30-s chair stand test, 40-m fast-paced walk and stair climbs test), and self-reported adherence compared to strengthening exercise.

Primary outcome measure:

Change in overall average knee pain assessed by visual analogue scale (VAS) over 12 weeks.

Pain will be evaluated at each time point using a 100 mm VAS and asked: “On this line, how would you rate your overall average knee pain in the last one week?” For knee pain assessed using VAS, terminal descriptors will be 0 mm = no pain to 100 mm = worst pain possible.

Secondary outcome measures:

1. Change in VAS knee pain over 24 weeks.
2. Change in WOMAC pain, WOMAC function, and WOMAC stiffness over 12 weeks and over 24 weeks.
3. Change in VAS knee pain over 12 weeks in patients with painDETECT > 12
4. Change in core physical performance measures as assessed by 30 s chair stand test, 40 m fast walk test, and stair climb test over 12 and over 24 weeks.
5. Change in Patient Health Questionnaire (PHQ-9) scales over 12 and over 24 weeks.
6. Change in patient global assessment score (assessed using a 100 mm VAS) over 12 and over 24 weeks.
7. Change in neuropathic pain, as assessed by the painDETECT questionnaire, over 12 and over 24 weeks.
8. Change in leg muscle strength will be assessed by leg muscle strength dynamometry at the lower limb (involving both legs simultaneously) over 12 and over 24 weeks.
9. Self-reported adherence to the yoga or strengthening exercise program from baseline to 12 and baseline to 24 weeks will be assessed using an online logbook and defined as the percentage of prescribed sessions undertaken.

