3. **Original Protocol:** We stated “the above sample size will allow us to detect a non-inferiority of yoga with strengthening exercise. Non-inferiority would be declared if the mean change in knee pain (assessed using VAS) in the yoga group was not significantly worse than the mean change in the strengthening exercise group, within a pre-stated margin of non-inferiority ( $\Delta$ ), in this case, set at 10 mm”.

**Open access protocol publication:** We stated “the above sample size will allow us to detect a non-inferiority of yoga with strengthening exercise. Non-inferiority would be declared if the mean change in knee pain (assessed using VAS) in the yoga group was not significantly worse than the mean change in the strengthening exercise group, within a pre-stated margin of non-inferiority ( $\Delta$ ), in this case, set at 10 mm”.

**Final Manuscript:** Since our study was powered for non-inferiority and has met the criteria for switching the trial objective from superiority to non-inferiority, as outlined by the European Agency for the Evaluation of Medicinal Products (EMA 2001), we conducted a non-inferiority analysis.

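### The non-inferiority rule is worded as absence of a significant difference, ties no confidence limit, level, time point or population to the 10 mm margin, and its stated 80% power does not fit the plan's own conventions

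*Combined protocol and SAP*

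**What the plan says.** The protocol (Sample Size calculation) and the SAP (Sample size calculation) give the same rule. It opens "Non-inferiority would be declared if the mean change in knee pain (assessed using VAS) in the yoga group was not significantly worse than" the change under strengthening exercise. The SAP's condition is that the mean change "in the yoga group was not significantly worse than the mean change in the strengthening exercise group, within a pre-stated margin of non-inferiority", and the size of the margin is given by the words "within a pre-stated margin of non-inferiority (D), in this case, set at 10 mm". The power claim follows: "Overall, 126 participants will give us 80% power to detect the non-inferiority of yoga compared with strengthening exercise".

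The superiority calculation in the same SAP section uses an MCID of 15 mm and a "two-sided significance level of 0.05, 90% power, and SD of VAS pain change 22.5, we will need a total of 98 participants". That total is then raised to 126 for about 20% dropout. No separate significance level is given for non-inferiority. The SAP's Data analysis section sets two-sided 0.05 and reports between-group differences with 95% confidence intervals. The section on the analysis used in the final manuscript repeats the two-sided 0.05.

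The primary outcome is VAS pain change over 12 weeks, with pain measured at weeks 4, 8 and 12. The protocol's Statistical Analyses section plans a treatment-by-time interaction followed by a main-effects model. The final-manuscript section estimates effects at each follow-up. Neither says which contrast is compared with the margin, and no analysis population is defined for VAS pain.

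Item 3 of the SAP summary of changes reports that, after a switch from superiority, "we conducted a non-inferiority analysis". It names no confidence level, time point or population.

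**The concern.** Non-inferiority is shown by rejecting the hypothesis that yoga is worse by the margin or more, so the whole confidence interval must lie on the favourable side of 10 mm. The plan's sentence instead makes a failure to find significance the evidence. It names the margin without saying whether the point estimate or the upper confidence limit must fall below it.

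Under the literal reading, a smaller or noisier trial passes more easily. Because the trial did move to a non-inferiority analysis, the rule governs a conclusion. A reader who wants to check that conclusion against the plan cannot tell which bound, level, time point or set of participants applies.

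**Working it through.** **Inputs.** Margin 10 mm, SD of change 22.5 mm, 126 participants and about 20% dropout (SAP, Sample size calculation); 1:1 allocation (protocol, Randomisation and blinding). Differences are yoga minus strengthening, so positive values mean that yoga is worse. SE = 22.5 × √(2/n per arm).

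| Evaluable | n per arm | SE (mm) | 10/SE |
|---|---|---|---|
| 126 | 63 | 4.009 | 2.494 |
| 126 × 0.8 = 100.8 | 50.4 | 4.482 | 2.231 |
| 98 | 49 | 4.546 | 2.200 |

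**Step 1: the superiority figure.** A two-sample t-test with 49 per arm, a 15 mm difference and two-sided 0.05 has 90.4% power, so 98 is reproduced. For dropout, 98/0.8 = 122.5, or 123. The plan's 126 is slightly generous (1 − 98/126 = 22.2%).

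**Step 2: the 80% non-inferiority power.** For a test that requires the upper confidence limit to be below 10 mm, with no true difference, power = Φ(10/SE − z).

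| Evaluable | One-sided 0.05 (90% CI), z = 1.645 | One-sided 0.025 (95% CI), z = 1.960 |
|---|---|---|
| 126 | Φ(0.849) = 80.2% | Φ(0.534) = 70.3% |
| 100.8 | Φ(0.586) = 72.1% | Φ(0.271) = 60.7% |
| 98 | 71.1% | 59.5% |

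The stated 80% appears only at one-sided 0.05 with all 126 evaluable. Under the 95% CI convention, 80% power needs 80 per arm: 160 evaluable, or 160/0.8 = 200 randomised.

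**Step 3: the literal rule.** Suppose that non-inferiority is declared whenever yoga is not significantly worse than zero at two-sided 0.05, that is, whenever the estimate is below 1.96 × SE. With yoga truly 10 mm worse, the chance of declaring it is Φ(1.96 − 10/SE).

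- 126 evaluable: Φ(−0.534) = 29.7%
- 100.8 evaluable: Φ(−0.271) = 39.3%
- 98 evaluable: Φ(−0.240) = 40.5%

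The error rises as the sample shrinks. Also requiring a point estimate below 10 mm changes nothing, because the cut-offs (7.86, 8.78 and 8.91 mm) are already below 10.

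**Step 4: the confidence-limit rule.** At a true 10 mm deficit, the 95% CI rule errs 2.5% of the time and the 90% CI rule 5%, at any sample size. With 126 evaluable, the largest estimate that passes is 10 − 1.960 × 4.009 = 2.14 mm for the 95% CI and 10 − 1.645 × 4.009 = 3.41 mm for the 90% CI. An estimate between these would pass one rule and fail the other, and the documents do not say which applies.

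**The case against.** The strongest reply is that the sentence does contain a margin. A test against zero needs none, and under the literal reading power at no true difference would be 97.5%, which does not fit the stated 80%. A margin-based test gives 80.2%. This stands as evidence of intent: the authors probably had a confidence-limit test in mind. It does not settle the matter, because the test that reproduces 80% is at a level that the plan states nowhere and ignores the plan's own dropout allowance.

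A reader might infer from the wording that a false non-inferiority claim was certainly far more likely than 2.5%. The documents do not support that. The test implied by the power figure has an error of 2.5% or 5%, and the summary of changes does not show that the loose rule was applied. An even looser reading, in which yoga need only be not significantly worse than the margin itself, is likewise ruled out: power at no difference would exceed 97.5%.

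A reader might also infer that poor adherence alone could produce non-inferiority, since adherence is collected ("defined as the percentage of prescribed sessions undertaken") but defines no analysis set for VAS pain. That does not follow.

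- Both arms are active, so missed yoga sessions could as easily make yoga look worse. The documents give no attendance data.
- Suppose, as an assumption, a 13 mm deficit in adherers, 70% adherence and no difference among the rest. The overall difference is 0.7 × 13 = 9.1 mm. With 50 per arm, SE = 22.5 × √(2/50) = 4.5, and the 95% CI rule passes with probability Φ(0.9/4.5 − 1.96) = Φ(−1.76), about 4%.
- Lack of a per-protocol set does not raise the error for the all-randomised difference, which is a defensible target in a pragmatic comparative effectiveness trial.

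It is also fair to say that two-sided 0.05, 95% intervals and a 12-week outcome all appear in the plan. What is missing is the sentence that ties them to the margin.

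**Conclusion.** The point holds as a defect in a stated decision rule. Taken at its words, the rule carries a false non-inferiority risk of about 30% (126 evaluable) to 40% (98 to 101) at a true 10 mm deficit. Taken as the power figure suggests, its level is unresolved between 2.5% and 5%, and the stated 80% becomes about 70% with 126 evaluable, or about 61% after 20% dropout, under the plan's 95% CI convention.

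These figures assume the plan's SD of 22.5 mm, normal approximations, no true difference for the power values, and no precision gained from baseline adjustment or from partial data on dropouts. The t-based power values are within one percentage point. Which rule was actually used cannot be determined from the documents.

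**What to change.** Replace the rule in both sample size sections, and state it with the non-inferiority analysis in the summary of changes:

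*Non-inferiority is concluded only if the upper limit of the two-sided 95% CI for yoga minus strengthening in VAS pain change at week 12, from the primary mixed model in all randomised participants, is below +10 mm.*

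Restate the power under that rule as about 70% with 126 evaluable and about 61% after 20% dropout. The alternative is to state openly that a one-sided 0.05 (90% CI) test is used, with 80% power before dropout and about 72% after. The first option matches the convention already written in the plan.

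An analysis based on the adherence logbook may be reported as supportive. It is a non-randomised comparison and should not have a veto over the main result.

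The cost is a short paragraph and a less favourable non-inferiority power than the plan now claims. No new data or model is needed for the main analysis.
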